# Effects of combined high-intensity aerobic interval training program and Mediterranean diet recommendations after myocardial infarction (INTERFARCT Project): study protocol for a randomized controlled trial

**DOI:** 10.1186/s13063-018-2529-3

**Published:** 2018-03-02

**Keywords:** Exercise design, Cardiorespiratory fitness, Low-volume training, Health status

## Abstract

**Background:**

Exercise therapy has long been used for rehabilitation purposes after myocardial infarction (MI) and the benefit of regular physical exercise is also well-established. High-intensity interval training (HIIT) has been proposed to be more effective than continuous exercise for improving exercise capacity and health-related adaptations to low-volume (LV) and HIIT are also known. Furthermore, the Mediterranean diet (Mediet) has been widely reported to be a model of healthy eating for its contribution to a favorable health status and a better quality of life, reducing overall mortality. This study will investigate the effects of different HIIT programs (high-volume [HV] vs LV) and Mediet recommendations in clinical condition, cardiorespiratory fitness, biomarkers, ventricular function, and perception of quality of life after MI, and compared to an attention control group that is recommended to Mediet and physical activity without supervision sessions.

**Methods/Design:**

In this randomized controlled trial, cardiorespiratory fitness, anthropometry, central and peripheral cardiovascular variables, biochemical and nutritional condition, and quality of life will be assessed before and after 16 weeks of intervention in 177 participants diagnosed with MI type 1. All participants will be randomly (1:1:1) assigned to the attention control group or two exercise groups (Mediet recommendations plus supervised aerobic exercise two days/week: (1) HV (40 min) HIIT group and (2) LV (20 min) HIIT group.

**Discussion:**

This study will be the first clinical trial comparing the effects of two different volumes of HIIT programs with Mediet recommendations for people after MI. The results of this study will provide good evidence for physical rehabilitation in this population.

**Trial registration:**

ClinicalTrials.gov, NCT02876952. Registered on 24 August 2016.

**Electronic supplementary material:**

The online version of this article (10.1186/s13063-018-2529-3) contains supplementary material, which is available to authorized users.

## Background

The term “myocardial infarction” (MI) may have major psychological and legal implications for the individual and society. It remains the principal cause of death and disability worldwide and is a measured outcome in clinical trials [1]. Hence, coronary heart disease is a chronic condition and patients are at high risk for new events and premature death. Several evidence-based interventions can improve prognosis. Thus, lifestyle changes should be explained and proposed to the patients before discharge, including cessation of smoking, blood pressure (BP) control, advice regarding diet and weight control, and the encouragement of physical activity. Exercise therapy has long been used for rehabilitation purposes and the benefit of regular physical exercise is also well-established [2]. It is known that exercise can improve both cardiovascular and non-cardiovascular parameters, such as improved anxiety, patient self-confidence, endothelial function, exercise capacity, cardiovascular efficiency, reduction in atherogenic and thrombotic risk factors, and perception of wellbeing have been described [2–6]; it is also included as an essential component for secondary prevention [7]. Furthermore, the risks of a well-designed supervised exercise program are very low [2, 8]. The intensity of aerobic exercise training is a key issue in cardiac rehabilitation programs [9]. Intensity ranges for aerobic training prescription and design are included in several guidelines and publications regarding secondary prevention and cardiac rehabilitation [9, 10]. Aerobic fitness is recognized as a robust indicator of cardiovascular health and a well-established predictor of total and cardiovascular mortality in people with and without coronary heart disease. Direct measurements of peak oxygen uptake (VO_2peak_) and ventilatory thresholds (i.e. VT1 and VT2) are considered the gold standard references for the evaluation of aerobic metabolism function and, consequently, for aerobic exercise intensity assessment and design [9, 11]. The increase of VO_2peak_ and VTs after a period of exercise training depends on the components of the FITT principle (i.e. frequency, intensity, time or volume, and type or modality), which constitute the key to achieve a safe exercise training effect. Endurance aerobic training is typically performed as continuous training at moderate-to-high exercise intensity in steady-state conditions of aerobic energetic yield. However, high-intensity interval training (HIIT) (i.e. repeated bouts of short duration, high- to severe- or severe- to extreme-intensity exercise, separated by brief periods of lower intensity) has been proposed to be more effective than continuous exercise for improving exercise capacity [9, 12–16]. Adding to that, health-related adaptations to low-volume and high-intensity interval training (LV-HIIT) have been presented. This type of training is characterized by sessions that involve a relatively small total amount of exercise at high intensity (i.e. ≤ 10 min) [17]. Previous studies have shown that LV-HIIT is an effective and time-efficient training strategy for improving insulin sensitivity, glucose control, and biomarkers of vascular function [18] and that training-induced adaptation for high-volume (HV) moderate-intensity continuous exercise and LV-HIIT protocols are strikingly similar [19]. Although contradictory results of the effect of HIIT in cardiovascular patients have been previously presented [20], to our knowledge there are no studies that compare HIIT with different volume exercise in a population that has suffered MI and compare that to an attention control group (AC) who is receiving only physical activity recommendations.

On the other hand, the relevance of overall high-quality food patterns, rather than focus on single nutrients and foods, has emerged as a powerful paradigm to address the diet and to assess their potential cardiovascular disease preventative effects [21]. The Mediterranean diet (Mediet), representing the dietary pattern usually consumed among the populations bordering the Mediterranean Sea, has been widely reported to be a model of healthy eating for its contribution to a favorable health status and a better quality of life, reducing overall mortality from cardiovascular diseases [22].

Considering all the above-mentioned points, the INTERFARCT study is designed to investigate what effect different 16-week supervised aerobic INTERval exercise programs (HV vs LV) with Mediet recommendations will have in people after suffering an acute myocardial inFARCTion compared to AC that is recommended a Mediet and physical activity without supervision sessions.

We hypothesize that: (1) supervised HIIT will get superior improvements in cardiovascular health than only physical activity recommendations; and (2) a high-intensity and LV exercise program will get similar results compared to a high-intensity and HV exercise program. Therefore, the primary objective of this randomized controlled trial (RCT) will be to assess the effects of different programs of HIIT and Mediet recommendations on overall health, cardiorespiratory fitness, biomarkers, ventricular function, and perception of quality of life after MI compared to only physical activity recommendations. The secondary objectives will be: (1) to analyze the differences in the studied variables between the two HIIT programs (HV vs LV) with Mediet recommendations to observe the effect of exercise volume; and (2) to analyze whether a treatment with only recommendations (exercise and diet) is effective in the secondary prevention of cardiovascular disease compared to supervised exercise.

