### Data analysis

The primary outcome variable of this study is VO_2peak_. A priori power analysis (G*Power 3 statistical software) [48] was performed to calculate the average sample size. Due to the lack of any source on the effect of VO_2peak_ in MI patients, we speculate a similar increase based on a study of coronary artery disease [49]. Therefore, we assume a mean change of 5.0 mL kg^−1^ min^−1^ and a common standard deviation (SD) of 4.0 for participants allocated to the HIIT groups and a mean change of 3.0 ± 4.0 mL kg^−1^ min^−1^ for participants allocated to the AC group. Based on 1:1:1 randomization to three treatment arms with equal group size, we expect that pre-post intervention differences in our design would be achieved with 177 people (59 each group, α = 0.05, Cohen medium effect size f = 0.23, 80% power). Assuming a maximum loss of follow-up of 10%, the plan will be to recruit a total of 194 individuals. The statistical analysis will be performed using IBM SPSS Statistics, Version 22.0 (IBM Corp., Armonk, NY, USA). In the final analysis, four comparisons will be made: HIIT groups vs AC; HV-HIIT vs LV-HIIT; HV-HIIT vs AC; and LV-HITT vs AC. Two parametric tests will be performed after all assumptions for each test are met. For comparisons between groups at baseline, one-way analysis of variance (ANOVA) or the non-parametric method of Kruskal–Wallis and Chi-square test will be used. A linear regression model with ANOVA will be used to assess training effects on the primary and secondary study outcomes. We will examine the delta (Δ) score for each group (AC, HV-HIIT, LV-HIIT), adjusting for age, sex, changes in body mass, and the initial value of each of the dependent variables. Helmert contrasts will be performed to analyze the difference between the two exercise groups pooled together and the AC group. Bonferroni correction was used to determine the level of significance when a significant main effect was found. The differences between dropouts and participants who remain in the study will be examined; the data will be analyzed according to the intention-to-treat principle [50]. For each outcome variable, the effect size and the level of significance corresponding to the main group (between-subjects), time (within-subjects), and interaction (group × time) will be reported. To prevent type I error, post hoc comparisons (pre vs post by group) will be performed when a significant interaction effect is present. Values will be expressed as mean ± SD. The significance level will be set at 5% (α = 0.05). Practical significance will be assessed by calculating Cohen’s *d* effect size. Effect sizes (*d*) > 0.8, in the range of 0.5–0.8, in the range of 0.2–0.5, and < 0.2 will be considered as large, moderate, small, and trivial, respectively.

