
## Discussion

A large-scale national Swedish registry study showed that the risk of cardiovascular events remained high in the first year post MI, indicating that those patients should be managed with effective prevention programs [51]. Therefore, one of the main challenges in secondary prevention after MI is the reduction in mortality and morbidity through evidence-based interventions [7]. In patients with stable angina pectoris secondary to coronary atherosclerosis, the review found that interval training improved cardiorespiratory fitness, endothelial and ventricular function, and morphology to a greater degree than conventional light- to moderate- and moderate- to high-intensity continuous aerobic training [9]. On the other hand, less is known regarding the effects of LV-HIIT, but growing evidence suggests this type of training stimulates physiological remodeling comparable with moderate-intensity continuous training despite a substantially lower exercise volume [17]. A recent study has shown that LV-HIIT exercise elicits similar cytokine and oxidative stress responses to steady-state at a high intensity higher volume exercise [52]. However, based on the review of the literature, several issues are still open to question and would benefit from further investigation in MI population:Does LV-HIIT provide similar benefits compared to HV-HIIT and is it associated with a lower risk of all-cause mortality in population after MI, being able to confirm that “less is more”?Which combination of treatment (Mediet recommendations + physical activity recommendation vs Mediet recommendations + supervised exercise) is most valuable in reducing cardiovascular risk in patients after MI?

The increase in the prevalence of heart disease and related co-morbidities is often associated with polypharmacy and disabilities, such as physical and emotional frailty. Non-pharmacologic management strategies including regular exercise and a healthy diet are necessary to get a comprehensive care plan for the whole disease. This study will be the first clinical trial comparing the effects of two different volumes of HIIT programs with Mediet recommendations for people after MI and also compared to an attention control group receiving only recommendations. The results of this trial will provide good evidence for physical rehabilitation in this population and what type of treatment achieves better physical results.

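### The plan hypothesises that low-volume and high-volume HIIT give similar results, but provides only a difference test, with no margin or confidence-interval rule that could support similarity

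*Protocol article*

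**What the plan says.** All references are to the protocol article.

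- **Background, hypotheses.** The first hypothesis is superiority of supervised HIIT over recommendations alone. The second is that "a high-intensity and LV exercise program will get similar results compared to a high-intensity and HV exercise program".
- **Background, objectives.** The matching secondary objective is worded the other way round: "to analyze the differences in the studied variables between the two HIIT programs (HV vs LV").
- **Data analysis, comparisons.** The plan states that "four comparisons will be made: HIIT groups vs AC; HV-HIIT vs LV-HIIT", followed by each HIIT arm against attention control (AC).
- **Data analysis, method.** "A linear regression model with ANOVA will be used to assess training effects on the primary and secondary study outcomes", applied to change scores with covariates. On level and multiplicity: "The significance level will be set at 5% (α = 0.05"), and "Bonferroni correction was used to determine the level of significance when a significant main effect was found". The number of comparisons over which Bonferroni divides is not given.
- **Data analysis, sample size.** A mean change of 5.0 mL/kg/min "and a common standard deviation (SD) of 4.0 for participants allocated to the HIIT groups", against 3.0 with SD 4.0 for AC; 59 per group, 177 in total.
- **Data analysis, effect size.** Cohen's d is to be reported, with values below 0.2 labelled trivial.
- **Discussion.** The first open question is "Does LV-HIIT provide similar benefits compared to HV-HIIT", linked there to confirming that less is more.

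**The concern.** The two hypotheses are of different types but receive the same analysis. A superiority hypothesis is supported when a difference test rejects. A similarity hypothesis is not supported when the same test fails to reject, because failure to reject may reflect only a wide interval. To support similarity, the plan needs a margin (the largest loss of benefit still to be called similar) and a rule comparing the confidence interval with it. The article has neither.

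The sample size does not help. It gives both HIIT arms a change of 5.0, so it rests on the contrast with AC, and the precision of the comparison between the HIIT arms was not considered.

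At stake is the claim that the shorter programme does as well as the longer one. If a non-significant result were taken as support, the claim would be easier to reach the less precise the trial is, and a multiplicity correction would make it easier still.

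**Working it through.** **Inputs (Data analysis section).** Mean changes 5.0, 5.0 and 3.0 mL/kg/min; SD 4.0 in every arm; 59 per arm; α = 0.05. Two-sided pairwise tests are my assumption, as sidedness is not stated. The SD is used unadjusted.

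**1. Reproduce the plan's figure.** The grand mean is 13/3 = 4.333. The between-group variance is [2 × (0.667)² + (1.333)²]/3 = 0.889, so f = √0.889/4 = 0.2357 (printed as 0.23). For a one-way F test with 2 and 174 degrees of freedom, λ = 177 × 0.2357² = 9.83 and power is 0.801. The 177 is therefore the size for an omnibus test in which the two HIIT arms are identical.

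**2. Precision of high-volume (HV) against low-volume (LV).**
- SE = 4.0 × √(2/59) = 0.736.
- 95% half-width = t(0.975; 174 df) × SE = 1.974 × 0.736 = 1.45 mL/kg/min.
- Relative to the assumed HIIT benefit of 5.0 − 3.0 = 2.0: 1.45/2.0 = 73%.

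**3. How often a real HV advantage of 1.0 (half the assumed benefit) would be non-significant.** Noncentral t, 174 df, noncentrality 1.0/0.736 = 1.36:

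| Level | Power | Non-significant |
|---|---|---|
| 0.05 | 0.271 | 73% |
| 0.05/3 = 0.0167 | 0.148 | 85% |
| 0.05/4 = 0.0125 | 0.125 | 88% |

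The last two rows assume a Bonferroni divisor of three or four.

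**4. What 59 per arm could support with a margin.** The article gives no margin, so these are assumed values. Non-inferiority, one-sided 0.025, true difference 0; power = Φ(margin/SE − 1.96):

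| Margin (mL/kg/min) | margin/SE | Power |
|---|---|---|
| 1.0 | 1.358 | 27% |
| 1.5 | 2.037 | 53% |
| 2.0 | 2.716 | 78% |

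A margin of 2.0 would concede the whole assumed benefit over AC, so it is a ceiling and not a candidate.

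**5. The Cohen's d label.** d = 0.2 at SD 4.0 is 0.2 × 4.0 = 0.8 mL/kg/min, well inside the half-width of 1.45. An observed d below 0.2 is compatible with a true difference larger than 0.8.

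**The case against.** **No stated misreading.** The article nowhere says that a non-significant result between the HIIT arms will be called similarity. The secondary objective is to look for differences, which a difference test serves, and less is more is posed as an open question. All of this stands, so it would be wrong to say that the plan commits to that reading. But the hypothesis is stated as one to be tested, and no planned inference could support it.

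**Gating.** A reader might infer that the two HIIT arms are compared only after a significant omnibus result. The text does not establish this. The four comparisons are announced without condition, the main-effect sentence concerns when Bonferroni sets the level, and the explicit interaction condition covers pre-post comparisons within groups. Gating is one reading only.

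**Similar to HV though no better than control.** If LV truly equals AC, so that HV leads by 2.0, the single HV against LV test misses 23% of the time at 0.05 and 42% at 0.0125. A reader might take these as the rate of a false similarity claim. They are not, because LV against AC is also tested. Simulating means 5, 3 and 3 with SD 4.0 and 59 per arm, HV against LV is non-significant while LV is significantly better than AC in about 1.7% of trials at 0.05 and 0.6% at 0.0125. This safeguard answers that scenario. It does not answer the partial loss in step 3, since LV beating AC does not show that LV matches HV.

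**Other evidence.** Cohen's d is planned, so the p-value is not the only information. It is, however, a label on a point estimate with no interval rule. Covariate adjustment may narrow the interval, but the article gives no correlation from which to say by how much, and adjustment would not supply a margin.

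**Left to an analysis plan?** The article itself fixes the comparisons, model, level and sample size. The point is that these do not fit the stated hypothesis.

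**Conclusion.** The concern holds in this form: the stated analysis can refute the second hypothesis but cannot support it, and the trial was not sized for it. With SD 4.0, 59 per arm and no covariate adjustment, the interval for the HIIT comparison is ±1.45 mL/kg/min, and a true loss of half the assumed benefit would go undetected about 73% of the time at 0.05 (85% to 88% if Bonferroni divides by three or four, which the article does not state).

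The documents do not support the stronger statements that non-significance will be read as similarity, or that the trial would readily declare LV similar to HV when it is no better than control. The primary objective and the sample size concern HIIT against AC, and this comparison is secondary. Severity: should be fixed.

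**What to change.** Keep the HV against LV difference test, which serves the stated secondary objective, and add the following:

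1. Report the adjusted LV minus HV difference in VO2peak change with its two-sided 95% confidence interval, whatever the omnibus result.
2. Before the data are analysed, fix and justify a non-inferiority margin smaller than the assumed 2.0 benefit. The documents offer no value; the 1.0 and 1.5 used above only illustrate the range.
3. Allow the word similar only if the lower bound lies above minus the margin; otherwise report the result as inconclusive.
4. State the power for the chosen margin at 59 per arm.

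Alternatively, reword the second hypothesis as exploratory estimation with a confidence interval and make no similarity claim.

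The cost is wording and, in the first option, one justified margin; no participants are added. The drawback is an openly low power for a secondary claim: at a margin of 1.0, about 73% of trials would be inconclusive even if the arms were identical. Recruitment was finishing at submission, so the margin has to be fixed promptly.

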## Methods/design

### Study design

INTERFARCT is a prospective, open-label, blinded-endpoint, three-arm, parallel RCT (ClinicalTrials.gov ID: NCT02876952) and fulfills the requirements of the Standard Protocol Items: Recommendations for Interventional Trials (SPIRIT) checklist [23] (Additional file 1). The Ethics Committee of the University of the Basque Country (UPV/EHU, CEISH, 2016) and the Ethics Committee of Clinical Investigation of Burgos University Hospital (CEIC 1462) have approved the study design, protocol, and informed consent procedure. All participants have to provide written informed consent before the clinical and physiological examination. Each participant will be given the opportunity to ask questions about the involvement in the trial and to have those questions answered by a researcher associated with the trial before providing consent. After baseline measurements, the participants will be followed for 16 weeks. All follow-up examinations will be performed in the same laboratory setting and by the same researchers as in the baseline measurements. After baseline testing, they will be enrolled in the trial given a trial-specific identification (i.e. INTERFARCT-1) number (ID). Allocation consignment was performed by one of the exercise physiologists who was not involved in the recruitment process. The participants were randomized to one of the three intervention groups (Attention Control [AC], HV High-Intensity Interval Training [HV-HIIT], or LV-HIIT) stratified by sex, body mass index (BMI), and age using a block and stratified randomization method and with a randomization ratio of 1:1:1. Medical staff will be blinded to participant randomization assignment. The trial will be conducted in the Cardiology Department at Santiago Apóstol Hospital, Miranda de Ebro, Burgos, Spain. A trial-specific ID number will be used when gathering and recording information about a participant. A list containing the contact details of all participants and their corresponding ID numbers will be kept separate from all other data. All paper copy forms will be stored in a locked cabinet in the hospital facility during the trial and only researchers involved in the trial will have access. Study data will be accessible by the researchers involved in the trial and only the principal investigator and investigators in the project will have access to data analysis.

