### Measurements

The measurements used in the protocol will be taken before and after the intervention period (16 weeks). The study protocol flow of participants is outlined in Fig. 1. The post-intervention test will be scheduled the following week after finishing the 16-week intervention period. The primary outcome variable is cardiorespiratory fitness, measured through VO_2peak_. The secondary outcome variables include left ventricular function, body composition, biochemical profile, vascular endothelial function, dietary adherence, the state of depression and anxiety, and health-related quality of life. The SPIRIT figure showing the respective time points for assessments and intervention is provided in Fig. 2.

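### BMI is a stratification factor in the randomisation but baseline BMI is missing from the outcome model: a small, conservative loss of precision that is almost free to repair

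*Protocol article*

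**What the plan says.** Under Study design, the article describes allocation to three arms "stratified by sex, body mass index (BMI), and age using a block and stratified randomization method" and "with a randomization ratio of 1:1:1". The BMI and age cut-points and the block size are not given.

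Under Data analysis, the model is set out: "A linear regression model with ANOVA will be used to assess training effects on the primary and secondary study outcomes". The change score is analysed by group, "adjusting for age, sex, changes in body mass, and the initial value of each of the dependent variables". This is a stated list of covariates that applies to every outcome, so the point does not depend on anything left to an analysis plan that is not shown.

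The two lists side by side:

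| Stratification factor | In the outcome model? |
|---|---|
| Sex | Yes |
| Age | Yes |
| BMI | No (only when BMI is itself the outcome, through its baseline value) |

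The article gives no reason for the difference.

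**The concern.** Blocking within BMI strata makes the arms more alike on BMI, which reduces the true sampling variability of a group contrast if BMI is prognostic. A model without BMI does not know this. It leaves BMI-related variation in the residual and reports a standard error as if BMI had been free to differ between arms by chance. Confidence intervals are then wider, and p-values larger, than the design warrants.

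The change in body mass does not close the gap. It is measured after randomisation, in participants who are weighed and counselled every two weeks (Mediterranean diet pattern) and of whom two thirds exercise under supervision. It may itself respond to the intervention, and it carries little information about which BMI stratum a participant started in.

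BMI is plausibly prognostic here. The investigators chose to stratify on it, the primary outcome is expressed per kilogram in the sample-size calculation, and the secondary outcomes include body composition and glucose, insulin and lipid measures. At stake is some precision and power, not validity.

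**Working it through.** **1. The plan's own figure.** The primary outcome: "The primary outcome variable is cardiorespiratory fitness", measured as VO2peak. Inputs from Data analysis: for the HIIT groups "we assume a mean change of 5.0" with "a common standard deviation (SD) of 4.0 for participants allocated to the HIIT groups", and for the control group "a mean change of 3.0 ± 4.0", all in mL/kg/min.

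- Group means 5, 5, 3 have mean 4.333. Their standard deviation is √[(0.667² + 0.667² + 1.333²)/3] = 0.943.
- Cohen's f = 0.943/4.0 = 0.2357.
- A three-group F test with noncentrality 177 × 0.2357² = 9.83 has power 80.1%.

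The stated 177 is therefore reproduced. The printed f of 0.23 is this value truncated; taken literally it gives 78.0% power at 177. The calculation uses an unadjusted SD, so it does not rely on BMI being in the model.

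**2. Effect of leaving BMI out, as an upper bound.** Let r be the correlation of baseline BMI with change in VO2peak after the planned covariates are accounted for. The article does not give r; 0 to 0.3 is an assumption. If stratification balanced BMI perfectly:

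- model SE / true SE = 1/√(1 − r²)
- actual two-sided α = 2 × [1 − Φ(1.960/√(1 − r²))]
- F-test power with BMI added uses f/√(1 − r²)

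Example at r = 0.3: √(1 − 0.09) = 0.954. The SE ratio is 1/0.954 = 1.048. The critical value is 1.960/0.954 = 2.055, so α = 0.040. The noncentrality is 9.83/0.91 = 10.8, so power is 83.9%.

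| Assumed r | SE overstated by | Actual α | F-test power with BMI (planned: 80.1%) |
|---|---|---|---|
| 0 | 0% | 5.0% | 80.1% |
| 0.1 | 0.5% | 4.9% | 80.6% |
| 0.2 | 2.1% | 4.6% | 81.8% |
| 0.3 | 4.8% | 4.0% | 83.9% |

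The last column is compared with the planned 80.1%. This slightly overstates what is forgone, because under perfect balance power without BMI also rises a little. In a pairwise comparison of 59 versus 59 at r = 0.3, power is 78.6% without BMI and 81.2% with it.

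**3. Simulation with imperfect balance.** Assumptions: N = 177, blocks of 6 within sex × BMI × age strata, BMI and age each cut in two, 80% in one sex category, no dropout. The contrast is pooled HIIT versus control, with a true difference of 0 (4,000 runs) or 2 with SD 4 (2,000 runs).

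| Assumed r | Type I error without / with BMI | Power without / with BMI |
|---|---|---|
| 0 | 4.7% / 4.7% | 89.3% / 89.2% |
| 0.1 | 5.6% / 5.6% | 87.0% / 87.3% |
| 0.2 | 4.6% / 5.0% | 88.2% / 89.0% |
| 0.3 | 4.5% / 5.2% | 88.6% / 90.8% |

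Monte Carlo error on the type I figures is √(0.05 × 0.95/4000) ≈ 0.3 points, so the 5.6% at r = 0.1 is noise around 5%. At r = 0.3 the average model SE without BMI was 0.640 against an empirical SD of 0.623, an overstatement of 2.8% rather than the 4.8% bound.

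A second simulation, with two or three BMI categories and Monte Carlo error of about 0.15 points, gave type I error without BMI of about 4.9–5.0%, 4.7–4.8% and 4.1–4.2% at r = 0.1, 0.2 and 0.3. Adding BMI raised power by about 0.3–0.5, 0.8 and 2 points respectively.

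**The case against.** The mismatch itself cannot be disputed, but its importance can.

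- **The correlation may be near zero.** What counts is what BMI adds after age, sex and baseline VO2peak per kilogram. The argument that body mass sits in the denominator concerns the level of VO2peak; the baseline value already absorbs much of that, and the outcome is the change. Obesity above 35 kg/m² is excluded (Table 1), which narrows the BMI range. This stands, and it is why the range must start at 0.
- **Perfect balance is not attained.** BMI has to be cut into categories to stratify, and some blocks end incomplete. The analytic figures are therefore upper bounds. This stands.
- **Planned power does not depend on BMI.** The 177 rests on an unadjusted SD of 4.0 and reaches 80.1% without it. What is forgone is a gain beyond the plan. This stands.

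A reader might infer that the 5% error rate is breached, that power is lost on every outcome, or that the trial is too small. The article supports none of these. Any departure from 5% is conservative. Nothing in the article ties BMI to change in, for example, HADS, SF-36, carotid intima-media thickness or D-dimer. The sample size reproduces from its own inputs.

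None of this gives a reason for leaving the factor out.

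**Conclusion.** The point holds as a minor inconsistency between design and analysis. One of three stratification factors is absent from a stated covariate list, and the post-randomisation change in body mass does not replace it. The treatment estimate remains unbiased and the false-positive risk is not raised.

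Confidence is high for the mismatch and for its direction where BMI is prognostic. The size is uncertain, because it rests on an assumed residual correlation of 0 to 0.3. Over that range the standard error is overstated by nothing to at most about 5%, and type I error runs from 5% down to about 4.0–4.5%. Power forgone is nil to about 2 points for pooled HIIT versus control, and up to about 4 points for the overall F test under perfect balance. For outcomes unrelated to BMI there is no effect.

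A reader might also take this as an argument for removing the change in body mass from the model. It is not one: whether to keep that covariate is a separate question, and adding baseline BMI does not settle it.

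**What to change.** In Data analysis, add baseline BMI to the covariates for the primary and secondary outcomes, either as a continuous variable or in the categories used to stratify, and state which. No addition is needed where BMI is itself the outcome, because its baseline value is already in the model. Leave the rest of the list as it is for the purpose of this point.

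The cost is one degree of freedom if BMI is continuous, or the number of categories minus one if categorical. No new data are needed, since BMI is part of the baseline anthropometry. The sample size does not change. The choice should be recorded before the group comparisons are run, so that it cannot look driven by the results.
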